### Trial design {8}

The MARBLE trial is a multicenter, randomized, open-label, parallel-group controlled trial designed to evaluate the superiority of ESBD over EST in terms of adverse event rate among patients receiving endoscopic transpapillary CBDS extraction. Patients diagnosed with small CBDS will be screened based on the inclusion and exclusion criteria. Eligible patients will be randomized at a 1:1 ratio to either the ESBD or EST groups.

The MARBLE trial has been designed and will be implemented by the TTSG, a multicenter consortium for clinical research, consisting of seasoned pancreatobiliary endoscopists from the Tokai region of Japan.

## Methods: participants, interventions, and outcomes

### Study setting {9}

This study is a multicenter collaborative trial that will be conducted at five tertiary referral centers located in the Tokai region of Japan. Specifically, the participating study sites are Aichi Medical University Hospital, Gifu University Hospital, Iwata City Hospital, Ise Red Cross Hospital, and Seirei Hamamatsu General Hospital.

### Eligibility criteria {10}

The inclusion and exclusion criteria are outlined in Table 2. Patients will be eligible for enrollment if they satisfy all of the inclusion criteria and none of the exclusion criteria. Key inclusion criteria are patients aged ≥ 18 years with CBDS confirmed by imaging, requiring endoscopic removal. Key exclusion criteria include stones ≥ 12 mm and previous papillary intervention. Endoscopic procedures for both groups will be performed by study endoscopists at each participating center. To ensure consistency across sites, all operators will participate in pre-study training and harmonization sessions, including review of procedural steps and photographic examples.

**Table 2 Tab2:** Eligibility criteria for participants with common bile duct stones in the MARBLE trial

Inclusion criteria*
1. Diagnosed with CBDS based on imaging such as CT, MRCP, abdominal ultrasound, or EUS
2. Judged to require endoscopic stone removal
3. Aged ≥ 18 years at the time of consent, regardless of gender
4. Provided written informed consent based on voluntary agreement after receiving sufficient explanation
**Exclusion criteria*******
1. CBDS with a stone diameter ≥ 12 mm
2. History of gastrointestinal reconstruction other than Billroth I
3. History of biliary reconstruction
4. Coexisting biliary strictures
5. Coexisting biliary tumors, including duodenal papillary tumors
6. Papillary orifice located within a periampullary diverticulum
7. Patients taking antithrombotic agents for whom medication cannot be discontinued or adjusted according to the Guidelines [5, 6] in patients on antithrombotic therapy
8. Bleeding tendency (platelet count < 50,000/mm^3^ or PT-INR > 1.5)
9. Coexisting severe cholangitis
10. Coexisting pancreatitis
11. History of any previous papillary intervention
12. Judged as unsuitable for endoscopic treatment due to safety concerns
13. Pregnant or possibly pregnant
14. Deemed ineligible for the study by the principal investigator or co-investigators

*CBDS* common bile duct stone, *CT* computed tomography, MRCP magnetic resonance cholangiopanreatography, EUS endoscopic ultrasound, PT-INR prothrombin time-international normalized ratio

^*^Eligible patients must meet all inclusion criteria and none of the exclusion criteria to be enrolled

### Who will take informed consent? {26a}

Trial investigators (endoscopists registered under the approved study protocol at each center) will provide participants with a detailed explanation of the study. Participants will be informed of study details in person by the investigator before enrollment, using both verbal and written explanations, and will have the opportunity to ask questions before signing consent. Written informed consent will then be obtained from each participant based on their voluntary decision, using the latest approved version of the consent form. This protocol has received IRB approval from all participating institutions.

### Additional consent provisions for collection and use of participant data and biological specimens {26b}

If the study data are to be used for secondary analyses in future research, additional approval will be obtained from the respective institutional review boards. Participants will be appropriately informed and given the opportunity to provide informed consent or to opt out. The MARBLE trial protocol does not involve the collection or use of biospecimens for research purposes.

## Interventions

### Explanation for the choice of comparators {6b}

EST is currently the standard first-line approach for papillary treatment during the management of small CBDS. As this study aims to evaluate the efficacy of ESBD as a novel alternative, EST is designated as the control intervention, and outcomes will be compared between patients undergoing ESBD and those receiving conventional EST.

### Intervention description {11a}

The procedure will be performed within 14 days of patient enrollment. A standard duodenoscope will be advanced into the duodenum, followed by biliary cannulation using a standard catheter and a 0.025–0.035-inch guidewire. A standard wire-guided sphincterotome will be used to perform EST. In the ESBD group, a minimal incision is made in the 11 to 12 o’clock direction without reaching the hooding fold. In the EST group, a medium incision extending beyond the hooding fold is performed. This standard will be reinforced through pre-study training and photographic documentation to ensure consistency among all operators. In the ESBD group, EPBD is subsequently performed with a diameter matching the lower bile duct (typically 6–10 mm). After completion of these procedures, stone removal will be performed using a retrieval basket and balloon catheter. Compared with conventional EST, ESBD is expected to reduce adverse event risk including bleeding.

### Criteria for discontinuing or modifying allocated interventions {11b}

Allocated interventions may be discontinued or modified after randomization under the following circumstances: if a patient voluntarily requests to withdraw from the study, if findings emerge after enrollment (including during the intervention) indicating that a patient should be excluded, if the study is terminated, or if the investigator determines that discontinuation is appropriate for any other reason. Patients who deviate from the protocol will remain in the intention-to-treat analysis; a per-protocol analysis will also be performed as sensitivity analysis.

### Strategies to improve adherence to interventions {11c}

To ensure adherence to the intervention protocol, all participating endoscopists will be provided with a standardized explanation of the procedural steps during a pre-study meeting. The meeting will serve as an opportunity to align procedural details such as the extent of sphincterotomy and balloon dilation techniques. In addition, study investigators at each site will ensure protocol compliance. Central monitoring and regular communication among centers will help identify and resolve any protocol deviations during the study period.

### Relevant concomitant care permitted or prohibited during the trial {11d}

Concomitant care and interventions are generally permitted at the discretion of the treating physician, provided they do not interfere with the study protocol. The use of antithrombotic agents will be managed according to the Guidelines [5, 6]. Antithrombotic agents may be withheld or adjusted as appropriate based on individual patient risk and in consultation with the prescribing physician.

### Provisions for post-trial care {30}

Participants who experience study-related adverse events will receive appropriate medical care in accordance with the study site’s standard medical practice. No specific ancillary or post-trial care is planned beyond the standard of care routinely provided at each participating institution. Although no specific post-trial care is planned, participants will be informed of the study results upon request, and late adverse events will be monitored during follow-up.

### Outcomes {12}

The primary outcome of this study is the incidence of procedure-related adverse events following endoscopic treatment. Secondary outcomes include the type and severity of adverse events, technical and clinical success rates, total procedure time, time required for stone removal, the need for lithotripsy, and long-term outcomes such as stone recurrence and biliary events during the 5-year follow-up period. The definitions of each outcome, along with their measurement variables, analysis metrics, and time points, are summarized in Table 1.

The definitions and severity grading of procedure-related adverse events will be defined according to the American Society for Gastrointestinal Endoscopy lexicon [7]. Among these, bleeding and pancreatitis are the most anticipated adverse events in this study and represent key safety outcomes; therefore, more detailed criteria are specifically defined for these two events. Intra-procedural bleeding is defined as bleeding that requires hemostatic intervention (excluding preventive measures), while post-procedural bleeding is defined as bleeding confirmed by endoscopy or imaging study such as computed tomography, or inferred from clinical findings such as hematemesis, melena, or a drop in hemoglobin level that cannot be explained by other causes. The diagnosis of pancreatitis is established when at least two of the following three criteria are met: (1) acute abdominal pain and tenderness in the upper abdomen, (2) elevated levels of serum or urinary pancreatic enzymes above the upper limit of normal, and (3) imaging findings indicative of acute pancreatitis [8]. Long-term outcomes, including stone recurrence over 5 years, will be monitored via periodic chart reviews and patient contact; imaging will be performed if clinically indicated.

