**Primary endpoint**			
Procedure-related AE rate	Proportion of patients experiencing procedure-related AEs after protocol intervention	Incidence proportion	Within 30 days from the procedure

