**Secondary endpoints**			
Type and severity of procedure-related AEs	Classified using ASGE lexicon; detailed criteria applied for bleeding and pancreatitis (see Notes)	Descriptive	Within 30 days from the procedure
Technical success rate	Completion of ESBD or EST according to protocol	Binary outcome	Day of procedure
Clinical success rate	Complete stone removal in a single session	Binary outcome	Day of procedure
Total procedure time	Time from cannulation to completion of stone removal	Continuous (minutes)	Day of procedure
Time required for stone removal	Time from end of ESBD or EST to completion of stone removal	Continuous (minutes)	Day of procedure
Proportion of cases requiring lithotripsy	Use of mechanical lithotripsy (excluding mechanical tools used without fragmentation), electrohydraulic lithotripsy, or laser lithotripsy	Incidence proportion	Day of procedure
Stone recurrence rate	Reappearance of bile duct stones post-removal	Incidence proportion	5-year follow-up
Time to stone recurrence	Days from successful stone removal to confirmed recurrence	Time-to-event	5-year follow-up
Biliary event rate	Any biliary event (e.g., stone recurrence, cholangitis, cholecystitis, liver abscess, biliary cancer)	Incidence proportion	5-year follow-up
Time to biliary event	Days from successful stone removal to occurrence of any biliary event	Time-to-event	5-year follow-up
**Notes on adverse event definitions** The definitions and severity grading of procedure-related adverse events will follow the ASGE lexicon [7]. Among these, bleeding and pancreatitis are the most anticipated adverse events in this study and represent key safety outcomes; therefore, more detailed criteria are specifically defined for these two events **-Bleeding:** *Intra-procedural bleeding*: requires hemostatic intervention (excluding preventive measures) *Post-procedural bleeding*: confirmed by endoscopy or imaging study such as computed tomography, or inferred from clinical findings such as hematemesis, melena, or a drop in hemoglobin level that cannot be explained by other causes **-Pancreatitis:** The diagnosis is established when at least two of the following three criteria are met: (1) acute abdominal pain and tenderness in the upper abdomen, (2) elevated levels of serum or urinary pancreatic enzymes, and (3) imaging findings indicative of acute pancreatitis [8]			

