## Assignment of interventions: blinding

### Who will be blinded {17a}

This is an open-label trial; therefore, neither participants nor treating endoscopists will be blinded to group allocation. Outcome assessors and data analysts will also not be blinded due to the nature of the intervention. However, to minimize bias in outcome evaluation, procedure-related adverse events will be classified and graded according to predefined criteria based on the American Society for Gastrointestinal Endoscopy lexicon, and all relevant outcomes will be objectively assessed using standardized metrics.

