### Plans to promote participant retention and complete follow-up {18b}

To ensure comprehensive follow-up and maximize participant retention, all patients will undergo clinical and laboratory evaluations on the day following the endoscopic procedure. Imaging studies such as computed tomography will be performed as clinically indicated.

Although no specific follow-up protocol is mandated during the post-treatment observation period, patients presenting with symptoms suggestive of adverse events will promptly undergo appropriate blood and imaging tests, following the same assessment principles used on the day after the procedure.

Long-term follow-up will continue until either the participant’s death or the end of the study’s follow-up period (i.e., 5 years after the final participant’s enrollment), whichever occurs first. Data collection during follow-up may include chart reviews, records from other institutions, or telephone interviews, as appropriate. Every effort will be made to obtain outcome data at the end of the study period whenever possible. A loss-to-follow-up rate of less than 10% will be targeted. To achieve this, we will maintain regular contact with participants through scheduled telephone calls and coordinate with referring hospitals for updated information. If the loss-to-follow-up rate approaches 10%, additional measures such as contacting family members or caregivers will be implemented.

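### Post-procedural bleeding may be inferred from a hemoglobin drop with no minimum size, baseline or window, so small falls can enter the primary endpoint on an unblinded investigator's judgement

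*Protocol article*

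**What the plan says.** The primary endpoint in Table 1 is "Proportion of patients experiencing procedure-related AEs after protocol intervention", counted within 30 days. Definitions and grading follow the ASGE lexicon, but for bleeding and pancreatitis the Outcomes section {12} adds that "more detailed criteria are specifically defined for these two events".

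Under those criteria, post-procedural bleeding is either confirmed by endoscopy or imaging, "or inferred from clinical findings such as hematemesis, melena, or a drop in hemoglobin level"; the last of these reads in full "a drop in hemoglobin level that cannot be explained by other causes". The Table 1 notes repeat this: "or inferred from clinical findings such as hematemesis, melena, or a drop in hemoglobin level that cannot be explained by other causes". Neither place gives a size, a reference value or a time window.

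Three other sections bear on how the rule will work:

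- Participant retention and follow-up {18b}: "all patients will undergo clinical and laboratory evaluations on the day following the endoscopic procedure".
- Who will be blinded {17a}: "Outcome assessors and data analysts will also not be blinded due to the nature of the intervention". The same section offers predefined lexicon-based criteria as the safeguard and says that "all relevant outcomes will be objectively assessed using standardized metrics". The abstract's Methods paragraph makes a similar claim.
- Adverse event reporting and harms {22}: site investigators collect and assess adverse events. No blinded or central adjudication is described.

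**The concern.** Confirmation and clinical inference are joined by "or", so confirmation is optional. Hematemesis, melena and a hemoglobin drop are alternatives, so the drop can stand alone. The only filter is whether another cause explains it. For a small fall that is a matter of opinion, and the person forming it knows whether the patient had EST or ESBD. The Intervention description {11a} also states the expected direction: fewer adverse events, bleeding included, with ESBD.

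The pancreatitis rule in the same paragraph shows the contrast. It needs two of three criteria and ties enzymes to the upper limit of normal. The hemoglobin route needs neither a second sign nor a limit.

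Two things are at stake. Applied evenly, surplus events dilute the difference and cost power. Applied more readily to EST, they can produce a superiority result where none exists.

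**Working it through.** **Inputs from the protocol.** Sample size {14}: 15.8% (EST) vs 4.4% (ESBD), two-sided α 0.05, power 80%, 1:1 allocation, 10% loss, 280 patients (140 per arm). Statistical methods {20a}: Pearson chi-square or Fisher's exact test; Pearson without correction is used below.

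**The plan's own figure.** With p̄ = (0.158 + 0.044)/2 = 0.101 and d = 0.114:

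- n = [1.96·√(2·0.101·0.899) + 0.842·√(0.158·0.842 + 0.044·0.956)]² / 0.114² = 108.5, so 109 per arm.
- With continuity correction: (108.5/4)·[1 + √(1 + 4/(108.5·0.114))]² = 125.4, so 126 per arm.
- 126/0.9 = 140 per arm, 280 in total.

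The stated target reproduces exactly. The sample size arithmetic is not in dispute.

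**Assumed input.** Let f be the share of patients, among those with no other primary event, in whom a hemoglobin-only event is accepted although there was no bleed. The observed rate is then q = p + (1 − p)·f. The documents give no value for f, so a range is shown. Rejection probabilities are exact enumerations of the chi-square test over the two binomial distributions.

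**Uneven acceptance, no true difference (p = 10% in both arms; the 10% is also assumed).**

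| f, EST vs ESBD | q, EST vs ESBD | False ESBD win, 126 per arm | 140 per arm |
|---|---|---|---|
| 0 vs 0 | 10.0% vs 10.0% | 2.5% | 2.4% |
| 2% vs 0.5% | 11.8% vs 10.45% | 5.2% | 5.4% |
| 5% vs 1% | 14.5% vs 10.9% | 13.2% | 14.4% |

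For example, 0.10 + 0.90·0.05 = 0.145.

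**Even acceptance, planning rates true.**

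| f, both arms | q, EST vs ESBD | Power, 126 per arm | 140 per arm |
|---|---|---|---|
| 0 | 15.8% vs 4.4% | 87.8% | 90.6% |
| 2% | 17.5% vs 6.3% | 80.0% | 84.0% |
| 5% | 20.0% vs 9.2% | 68.8% | 74.0% |

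For example, 0.158 + 0.842·0.05 = 0.200 and 0.044 + 0.956·0.05 = 0.092.

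**What a threshold would do (illustration only).** Assume a non-bleeding next-day change that is normal with mean fall 0.3-0.5 g/dL and SD 0.5-0.7 g/dL. Then P(any fall) = Φ(mean/SD) runs from Φ(0.3/0.7) = 67% to Φ(0.5/0.5) = 84%. P(fall ≥ 2 g/dL) runs from 1 − Φ(1.7/0.5) = 0.03% to 1 − Φ(1.5/0.7) = 1.6%. These means and SDs are assumptions and do not feed the tables above.

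**The case against.** **The rule has a filter.** Fluids, blood sampling and assay variation are themselves other causes, so on its plain wording the rule lets an investigator discount an ordinary fall, and the event must also be procedure-related. This stands against the stronger reading that ordinary next-day decreases will become events; the text supports only that they can. It does not remove the concern, because the filter is the unblinded judgement.

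**A limit may exist elsewhere.** The cited lexicon or the full protocol may hold one, and neither is at hand. But the trial's own bleeding criteria are spelled out twice, and neither place states a limit or points to one for this route. If one is meant to apply, saying so takes one sentence.

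**Hemoglobin is not named among the next-day tests.** True. Its inclusion is a reasonable inference, not a stated fact. How often it falls without bleeding is likewise assumed.

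**The bleeding share does not measure exposure.** A reader might note that bleeding supplies 7.9 − 0.9 = 7.0 of the 15.8 − 4.4 = 11.4 points of planned effect and infer that all 7.0 are at risk. The Background figures do not support that. They cover all bleeding and are not split by route of diagnosis, and intra-procedural bleeding has its own requirement for a hemostatic intervention. The exposed share is unknown.

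**The harm may be small.** At 2% vs 0.5% the false-win chance is about 5%, and an even 2% leaves power at the 80% target or above. This stands, and is why a range is given.

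**Severity by arm is already reported.** Type and severity form a secondary endpoint, but nothing there separates hemoglobin-only events from overt or confirmed bleeds.

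**Conclusion.** The concern holds in a limited form. The stated bleeding rule lets a hemoglobin fall of any size, without overt bleeding or confirmation, count towards the primary endpoint if an unblinded site investigator sees no other cause. That falls short of the objective criteria on which the blinding section and the abstract rely.

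Under the assumed acceptance rates, the chance of a false ESBD win rises from the nominal 2.5% to about 5-14%. If acceptance is even at 2-5%, power falls from 91% to 84-74% with 140 per arm, or from 88% to 80-69% with 126 per arm. The documents fix neither the acceptance rates nor the 10% null rate, so these figures show what the wording permits and are not a forecast. The target of 280 is correctly computed and is not affected.

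**What to change.** In Table 1 and the Outcomes section:

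1. For a hemoglobin-only event, prespecify a minimum fall from the last pre-procedure value within a stated window. A fall of 2 g/dL is one example. It has no basis in the documents, so the sponsor should set the value or state that a limit in the cited lexicon applies.
2. Count smaller falls only with hematemesis, melena, or confirmation by endoscopy or imaging.
3. Record the route of diagnosis for each bleeding event and tabulate hemoglobin-only events by arm.
4. Repeat the primary analysis without hemoglobin-only events as a sensitivity analysis.

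The cost is a sentence or two in the endpoint definition, one case report form field and one extra analysis. Recruitment is scheduled to run to 31 March 2027, and the protocol has an amendment route that covers changes to outcomes and analysis methods. The downside is that a few small unconfirmed bleeds no longer count. A threshold also does not remove all discretion: for larger falls, the question of other causes still rests with an unblinded investigator.

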### Participant timeline {13}

A schematic diagram of the time course and schedule for participants of the MARBLE trial is illustrated in Fig. 1.

**Fig. 1 Fig1:**
[figure not shown]
Time schedule of enrolment, interventions, and assessments in the MARBLE trial. ●: Required 〇: To be performed as necessary. *ESBD*, minimal endoscopic sphincterotomy with balloon dilation; *EST*, endoscopic sphincterotomy; *AE*, adverse event

### Sample size {14}

The sample size estimation was based on a two-sided chi-square test. A previous retrospective study comparing ESBD and EST reported that the incidence of procedure-related adverse events was 15.8% in the EST group and 4.4% in the ESBD group [3]. Based on these findings, a sample size calculation was performed using a two-sided test with a significance level (*α*) of 0.05 and a power of 80%, assuming a 1:1 allocation ratio. Accounting for an estimated 10% of ineligible or dropout cases, the final target sample size is set at 280 patients (140 in each group). In addition to the primary sample size estimation based on retrospective data, a sensitivity analysis will be performed using alternative event rates reported in other studies to ensure the robustness of the calculation.

